##### Childcare Quality

The lead teacher in each classroom reports features of the childcare such as type of care, group size, staff-to-child ratio, and characteristics of the child group and staff.

CLASS toddler version [31,32] is used to evaluate process quality. CLASS provides relevant, valid, and reliable information about child–caregiver interactions [31]. Each unit is observed by the CLASS observers for three 15-minute periods (preintervention, midintervention, and postintervention) as well as during a follow-up 1 year later (only the intervention group).

The quality of teacher–child relationships (ie, children’s relationship with teacher) as perceived by the teacher is assessed through 3 dimensions, namely, closeness, conflict, and dependency, using The Student–Teacher Relationship Scale, Short Form (STRS-SF) [33,34], which consists of 15 items.

Life in Early Childhood Programs (LECP) measures the atmosphere, routines, and rhythms of the group [35]. The LECP asks teachers about the degree of control and organization (degree of consistency or routines, if objects or toys are put in the same place), the use of space, contextual traffic (if many people are coming and going), and group density. A higher score on the LECP indicates a higher level of chaos in the group.

##### Child Outcomes

Children’s development and mental health outcomes are determined by serval measures, gathered from both parents and 1 selected staff member working with each participating child.

The Brief Infant Toddler Social and Emotional Assessment (BITSEA, parent and teacher report) [36] is used to map children’s social/emotional/behavior problems and delayed development across 4 domains: externalizing, internalizing, dysregulation, and competence.

Caregiver–Teacher Report Form (C-TRF, teacher report) and Child Behavior Checklist (CBCL, parent report) from the Achenbach System of Empirically Based Assessment (ASEBA) from 1.5 to 5 years [37] are checklists used for mapping emotional difficulties and behavior problems in children. The checklist measures symptoms of anxiety/depression, somatic disorder, withdrawnness, attention difficulties, and aggressive behavior, as well as overarching internalizing and externalizing behaviors. In addition, the Language Development Survey (LDS) is included as part of CBCL for parents to measure which words children use. LDS is answered by mother, father, and teacher for this study.

Leiden Inventory for Child’s Well-Being in Day Care (LICW-D) [38] measures the child’s socioemotional well-being in daycare with 12 items (eg, enjoys attending, feels at ease in the group, not difficult saying goodbye to parents). Mother, father, and teacher answer these questions in this study.

Secure Base Safe Haven Observation Unit (SBSHO) [39] measures children’s secure attachment to their caregiver. Through 20 questions, parents and the child’s key person in the group are asked to evaluate to which degree the child uses them as a secure base.

#### Secondary Outcome: Child Cortisol Levels

Child cortisol levels are assessed in a subsample of 300 children who enter childcare for the first time. The tests are done in the childcare center at 10 am and 3 pm and at home at 6 pm for 2 days at T1 (the average is calculated). At T2, cortisol levels are assessed at 10 am and 3 pm for 2 days in the center and 2 days at home during a weekend (the average for every point in time). At T3, measures are taken in the same way as T1. The collection, storage, and evaluation, including the placement of the material, are approved by Regional Committees for Medical and Health Research [40], reference number 2017/430 [40].

#### Implementation Outcomes

##### Fidelity

Fidelity to the intervention is measured through checklists and self-reporting [41]. Class attendance and attendance in monthly supervision sessions is registered. The supervisors rate their own fidelity of intervention on a 5-point Likert scale (from minimal to high) through questions such as “I helped use the CLASS dimensions and relational quality when the supervisor reflected on practice,” “I focused on how the supervisor could develop as a mentor for their staff.”

##### Acceptability

Acceptability (ie, the users’ satisfaction with various aspects of the intervention) is measured by self-report and focus group interviews with parents and staff at the end of the intervention period.

##### Sustainability

Sustainability is to be measured through semistructured interviews and self-report at the end of the intervention period and at 1-year follow-up [41].

#### Background Variables

##### Child Factors

Serval measures and questions are used to gauge children’s background, including the child’s personal characteristics and aspects of their environment.

The Early Childhood Behaviour Questionnaire, Short Form (ECBQ) [42] measures children’s temperament, including reactive processes that involve emotions, motor and sensory systems, and self-regulation processes that control reactivity.

The Emotionality, Activity, Sociability Temperament Survey for Children (EAS) [43] measures 4 dimensions of the child’s temperament (emotionality, activity, sociability and shyness) on 5 items.

More general characteristics and childcare history are obtained through questionnaire data detailed by parents (eg, number of siblings, preterm, ethnicity, disabilities, when they started kindergarten, how many kindergartens they have attended).

##### Family Factors

Parents report on their own background such as their ethnicity, country of origin, marital status, education, and family socioeconomic status through information about parental income.

##### Childcare Factors

Leaders of the childcare centers report on the organization and size of the childcare center, as well as staff turnover and sick leave. Childcare staff report their gender, ethnicity, age, education, and experience working in childcare. Childcare staff also report on their level of occupational stress and well-being at work, their motivation, and receptiveness to changes in the workplace.

#### Recruitment and Participation

Recruitment and participation data will be reported for available data from baseline.

#### Participant Retention

Contact with childcare staff is maintained by the research group through meetings and emails. Contact with participating families (parents) is maintained mainly by childcare staff. Reminders to fill out questionnaires are sent via email or SMS text messages.

To reduce dropout in the control groups after randomization, childcare centers in the control group receive a gift certificate of 3000NOK (US $336.60) to buy material for their childcare center and are offered the intervention 1 year after the intervention group.

#### Data Management

Observational data are collected by CLASS toddler–certified observers. Questionnaire data are collected and managed by an independent data collection team at the primary sponsor site (Centre for Child and Adolescent Mental Health [RBUP] East and South). The independent data collection team is responsible for monitoring the data as they are collected, as well as checking that the data are consistent and free from errors. Data analysis and cleaning will be performed by study investigators. Data are stored on a secure server at the primary sponsor site during the study and analysis of results. Project staff will have access to the final trial data set. Following the study, data will be anonymized and archived according to Norwegian law.

#### Data Analysis

The study is carried out in toddler groups in childcare centers. Thus, data analyses will be conducted in a multilevel modeling framework to account for nonindependence of the participants at center level.

#### Sample Size and Power

Sample size and power was calculated using SPSS SamplePower (IBM). Based on previous studies [6], we choose a conservative estimate of expected effect of 0.30 (Cohen *d*). With a power of 0.80 and α=.05, we need 352 individuals if the randomization was performed individually. We plan to include data from 16 children from each childcare center. In a similar research [44], the intraclass correlation coefficient (ICC) was reported to be approximately 0.05. However, because several children will be evaluated by the same caregiver, we estimate with an ICC as high as 0.10. The resulting design effect with ICC=0.05 (or 0.10) D=1.75 (or 2.5), and the total required sample size is Nc=352 × 1.75 = 616 (or 352 × 2.5 = 880) individuals. We plan to include 1100 individuals, and 1100/16=69 childcare centers, to account for possibly 20% missing data on individual level, and uncertainty in the effect size and ICC. The planned selection will be in accordance with the Consolidated Standards of Reporting Trials (CONSORT) guidelines for clustered randomized trials [45].

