For toddler groups (ages 1-3) we found a small but significant increase in quality from pre to post in the Emotional and behavioral support domain (mean 5.97 [SD 0.41] vs mean 6.08 [SD 0.38]; *t*_103_=–2.45; *P*=.02) but not in the Engaged support for learning domain (mean 3.24 [SD 0.76] vs mean 3.44 [0.77]; *t*_103_=–1,86; *P*=.07). For the Pre-k groups (ages 3-5), there was a significant increase in quality from pre to post measures across all 3 domains: Emotional support (mean 6.06 [SD 0.56] vs mean 6.20 [SD 0.43]; *t*_127_=–2.56; *P*=.01), Classroom organization (mean 5.27 [SD 0.76] vs mean 5.55 [SD 0.66]; *t*_127_=–3.38; *P*=.001), and Instructional support (mean 2.67 [SD 0.84] vs mean 3.02 [SD 0.98]; *t*_127_=–3.40; *P*=.001). Moreover, qualitative interviews with center leaders, head teachers, and staff from the first cohort (N=53) revealed great satisfaction with the quality-building framework and the holistic approach to quality building. Overall, they reported feeling more competent in their day-to-day interactions with the children and highlighted that the intervention had given all staff on different levels shared knowledge and a shared language to talk about quality with colleagues. There were, however, also several challenges. Most importantly, staff needed more time than predicted to fully comprehend the CLASS framework and content of the specific dimensions. The supervisors did not receive enough support and reported lacking a manual/written material to help structure the supervision throughout the intervention period.

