### Outcomes

#### Data Collection

Data are collected at four points: T1 (preintervention), T2 (midway assessment), T3 (postintervention), and T4 (1-year postintervention follow-up). Participants from the intervention and control centers (parents, childcare staff, and group leaders) are sent links to the questionnaire via SMS text message or email. Each child is given unique, confidential identifiers to log-in and answer questions about the child (by the parent/staff). Both parents and 1 selected staff member working with each participating child are asked to fill out the questionnaires about the child. In addition, parents and childcare staff answer questions about themselves, and the staff about aspects of the center they work in. Each unit in the participating centers (both intervention and control centers) is also observed by trained CLASS observers at the following periods: preintervention, midintervention, postintervention, and during a follow-up 1 year later (only the intervention group).

T1 took place in September and October 2018 with CLASS observations in 187 units (both the control and intervention groups, with only the intervention group receiving feedback) and questionnaires to all staff and parents. T2 took place in January 2019 with new CLASS observations but no questionnaires. T3 took place at the end of the intervention (1 childcare year) in May/June 2019 with CLASS observations and questionnaires to all staff and parents. In addition, qualitative interviews will be conducted at T3. At 1-year follow-up after the intervention (T4) the intervention group is observed with CLASS and questionnaires will be filed out by all staff and parents (Textbox 1).

Study outcomes and measures used for Thrive by Three.

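### The 80% power at d = 0.30 is a child-level figure; for CLASS, a primary outcome scored once per toddler group in 187 groups, power at that effect is about half

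*Protocol article*

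**What the plan says.** The Sample Size and Power section of the protocol article takes its effect from previous studies: "we choose a conservative estimate of expected effect of 0.30" (Cohen d). "With a power of 0.80 and α=.05", it concludes that "we need 352 individuals if the randomization was performed individually". The cluster size is also in children: "We plan to include data from 16 children from each childcare center". ICCs of 0.05 and 0.10 give design effects of 1.75 and 2.5 and totals of 616 and 880. The plan is for 1100 children in 69 centers, "to account for possibly 20% missing data on individual level, and uncertainty in the effect size and ICC".

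The Abstract and the Outcomes section name CLASS, STRS-SF and LECP as primary measures of childcare quality, ahead of the child outcomes. CLASS is an observation of the toddler group, and the Data Collection section reports "CLASS observations in 187 units" at T1. The Randomization section says that centers were randomized. The Pilot Study section reports toddler-group CLASS means before and after the intervention: "mean 5.97 [SD 0.41] vs mean 6.08 [SD 0.38"] for Emotional and behavioral support, and 3.24 (SD 0.76) versus 3.44 (SD 0.77) for Engaged support for learning.

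**The concern.** Every input to the calculation is a child-level quantity: individuals, children per center, an ICC raised because one caregiver rates several children, and missing data per individual. The first primary aim, however, is the quality of caregiver–child interactions, and CLASS yields one assessment per group at each time point. The plan's own figure is 352 independent observations for d = 0.30, and CLASS supplies 187 before any allowance for groups sharing a center.

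The study hypothesis puts childcare quality and child outcomes in one superiority statement, and only one power figure is given. A reader can easily carry the 80% over to CLASS. A non-significant CLASS result might then be read as evidence that the intervention does not raise quality, when the test had roughly an even chance of detecting the assumed effect.

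**Working it through.** **Inputs from the protocol article.** d = 0.30, power 0.80, α = 0.05, 352 individuals, 16 children per center, ICC 0.05 or 0.10, 20% missing data, 1100 children and 69 centers (Sample Size and Power); 187 units (Data Collection); pilot means, SDs and t values on 103 df (Pilot Study).

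**Assumptions.** Two-sided test (a one-sided test does not reproduce 352), 1:1 allocation, 69 centers, no loss of groups. The protocol's ICCs describe children within centers; using them for group scores is also an assumption.

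**1. The plan's own figure.** A two-sample t test with d = 0.30 and 176 per arm has power 0.801, so N = 352. Design effects: 1 + 15 × 0.05 = 1.75 and 1 + 15 × 0.10 = 2.5. Totals: 352 × 1.75 = 616 and 352 × 2.5 = 880. Then 880/0.80 = 1100 and 1100/16 = 68.75, or 69 centers. Everything reproduces.

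**2. The same test for CLASS.** Groups per center: m = 187/69 = 2.71. Design effect: D = 1 + (m − 1) × ICC. Effective N = 187/D. Power and detectable difference come from the noncentral t, unadjusted:

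| Center ICC for group scores | D | Effective N | Power at d = 0.30 | Detectable d at 80% power |
|---|---|---|---|---|
| 0 | 1.00 | 187 | 53% | 0.41 |
| 0.05 | 1.09 | 172 | 50% | 0.43 |
| 0.10 | 1.17 | 160 | 47% | 0.45 |
| 0.20 (assumed) | 1.34 | 139 | 42% | 0.48 |
| 0.30 (assumed) | 1.51 | 124 | 38% | 0.51 |

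Taking the pilot's pre-intervention SDs, 0.41 to 0.45 SD is about 0.17 to 0.18 points on Emotional and behavioral support (× 0.41) and 0.31 to 0.34 points on Engaged support (× 0.76).

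**3. Sensitivity to the number of centers.** If there were about 96 centers (1531 recruited children/16), m = 1.95. Power is then about 50% at ICC 0.10 and 44% at 0.30. At ICC 0 the number of centers makes no difference.

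**4. Adjustment for the T1 score.** The SD of the pilot change is (difference/t) × √104, and r = (SD₁² + SD₂² − SD_change²)/(2 × SD₁ × SD₂).
- Emotional and behavioral support: 0.11/2.45 × √104 = 0.458, so r ≈ 0.33. Rounding of the means matters: differences of 0.10 and 0.12 give r of 0.45 and 0.20.
- Engaged support: 0.20/1.86 × √104 = 1.097, so r ≈ −0.03, in effect zero.

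Dividing the effective N by (1 − r²) with r = 0.33 gives power of 58% at ICC 0 and about 52% at ICC 0.10. With r ≈ 0 nothing changes. Reaching 80% at d = 0.30 would need r of about 0.68 even with no center clustering.

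**5. Pilot gains in SD units.** 0.11/0.41 = 0.27 and 0.20/0.76 = 0.26. Unadjusted power at these effects and ICC 0 is 45% and 43%.

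**The case against.** The section speaks of individuals and children and never says in terms that CLASS has 80% power. Its arithmetic is right, and recruitment (1531 children) exceeded the plan. STRS-SF, another primary quality measure, is a child-level rating, so the calculation can apply to it and the quality aim is not wholly uncovered. All of this stands, and it makes the defect one of scope. None of it adds a CLASS observation.

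Four stronger readings are tempting, and the article does not support them:

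- **That LECP has the same shortfall.** LECP describes the group, but teachers answer it and the number of raters per group is not stated. The figures above apply only if there is one report per group. If all 769 staff answered (69 centers, d in SDs of individual ratings), power would be about 92%, 83%, 67% and 54% at ICCs of 0.05, 0.10, 0.20 and 0.30.
- **That CLASS power is as low as 38%.** This needs a center ICC for group scores of about 0.3, which the article does not give.
- **That the missing-data allowance consumes the whole margin**, because 880/0.80 is exactly 1100. The cited ICC is about 0.05, for which 616/0.80 = 770 would do. Planning at 0.10 therefore carries a margin of 330 children.
- **That 0.30 is shown to be too optimistic.** The pilot gains are uncontrolled pre–post changes under a version with less written material and no mentor supervision of supervisors. They do not estimate this trial's between-arm effect, and the gap from 0.30 is small. What can be said is that 0.30 is not conservative relative to those gains.

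**Conclusion.** The concern holds for CLASS. The stated 80% at d = 0.30 covers child-level outcomes and does not carry over to an outcome with 187 group scores. With 1:1 allocation and no loss of groups, CLASS power at that effect is at most about 53% unadjusted, and about 47% to 50% at the protocol's own ICCs with 69 centers. The detectable difference is about 0.41 SD at ICC 0 and 0.45 SD at ICC 0.10. T1 adjustment helps modestly for Emotional and behavioral support and not at all for Engaged support, judged by the pilot. The shortfall against 80% depends neither on the assumed ICC nor on the number of centers, since it is present at ICC 0; those two assumptions only set how far below 53% the unadjusted power falls.

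**What to change.** In Sample Size and Power:

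- State that 80% power at d = 0.30 refers to child-level outcomes only.
- Add the CLASS power or detectable difference from 187 groups nested in centers, using the actual number of centers randomized and labelling the ICC as an assumption. On present information this is about 0.41 to 0.45 SD for ICC 0 to 0.10. If a T1-adjusted figure is given, give it by CLASS domain.
- Note that the effect of 0.30 is not conservative relative to the pilot's uncontrolled CLASS gains of 0.26 to 0.27 SD.
- State how many LECP reports there are per group, so that its power can be placed.
- Say that a non-significant CLASS result will be interpreted by its confidence interval.

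This is a change of text only, with no extra recruitment or data. The cost is a less favorable stated power for CLASS.

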#### Planned Statistical Analysis

To determine the effect of the intervention regression analyses, mixed model analyses or structural equation modeling as appropriate will be conducted, taking into account the clustered or multilevel structure of the data and data related to background factors. Because children are of different ages at study enrollment, some children will stay in intervention classrooms for 2 years, while some for just 1. We will adjust for child age in the analyses to account for these differences in “treatment exposure.” Missing data will be estimated in the models using a well-established technique that allows for the inclusion of all available data and estimation of missing values.

#### Qualitative Analysis

Qualitative analysis of interviews will focus on meaning of texts [46]. Elements from the thematic analysis will therefore be used to analyze the interviews [47]. Analysis will first focus on identifying relevant codes in the text [46]. The next phase will involve sorting the codes into potential overarching themes. The themes will then be reviewed and refined using constant comparative methods to reduce data into essential concepts and relationships. Internal homogeneity and external heterogeneity among themes will be considered in this phase. Three coders will independently categorize the interviews and their coding will be combined [48].

#### Cost

The costs of the intervention will be evaluated by calculating the hours that childcare staff, leaders, CLASS observers, and mentors have donated to the project in relation to the number of toddler groups and children exposed to the intervention. An estimate of per-child cost will be included in the final report to funders, along with additional estimates of costs incurred by the trial research team.

### Availability of Data and Materials

The data sets or other material used during this study are available from the principal investigator ([name]) on reasonable request.

### Ethics Approval and Consent to Participate

Ethics approval for the study was given by Regional Committees for Medical and Health Research [40], reference number 2017/430 [49]. We anticipate low risk of harm for participating in the intervention since the work on employee process quality is based on literature and previous research that have shown to be positive for children’s development. In addition, education and guidance for employees is not likely to be harmful for children’s development. Consent was given written by municipalities, childcare centers, and parents. Childcare centers volunteered to participate. All parents of children in the toddler groups of the participating childcare centers were invited to participate and gave a written consent. Consent was given by childcare staff throughout the year.

## Results

### Trial Status

As of August 2020, in total, 1531 children and 769 staff from 187 toddler groups have been recruited. Due to turnover, staff recruitment will be ongoing until August 2020. As of January 2020, the intervention group has been working with Thrive by Three for 1.5 years. Data collection at T1, T2, and T3 from both the intervention and control groups has been completed and T4 will be completed in August 2020. We expect to find an increase in childcare quality and better mental health and development outcomes for children in the intervention group. The reporting of these results will be made in accordance with the CONSORT guidelines [45]. The trial began recruitment in February 2017 and finished in August 2018. Data collection will finish in August 2020.

### Changes to the Protocol

Changes to the project are made in the standard operating procedure. These changes are recorded and maintained by the principal investigator for RBUP East and South. Changes which are merely procedural but may impact the experience of the participants in the study are reported to the Regional Committees for Medical and Health Research ethics for approval.

